## Abstract

**Introduction:**

Our aim is to investigate whether a shortened digital self-care intervention is non-inferior to, and cost-effective compared with, a comprehensive and therapist-guided cognitive behavioural therapy treatment for atopic dermatitis (AD).

**Methods and analysis:**

This is a single-blind, randomised clinical non-inferiority trial at Karolinska Institutet, a medical university in Stockholm, Sweden. We will recruit 174 adult participants with AD through self-referral. Participants will be randomised 1:1 to the two experimental conditions. Participants randomised to guided care will receive internet-delivered cognitive behavioural therapy for 12 weeks. Participants randomised to digital self-care will have access to this self-guided intervention for 12 weeks. At post-treatment (primary endpoint), non-inferiority will be tested and resource use will be compared between the two treatment groups. Cost-effectiveness will be explored at 1-year follow-up. Potential mediators will be investigated. Data will be analysed intention to treat. We define non-inferiority as a three-point difference on the primary outcome measure (Patient-oriented Eczema Measure). Recruitment started in November 2022.

**Ethics and dissemination:**

This study is approved by the Swedish ethics authority (reg. no 2021-06704-01) and is preregistered at ClinicalTrials.gov. The study will be reported according to the Consolidated Standards of Reporting Trials statement for non-pharmacological trials. The results of the study will be published in peer-reviewed scientific journals and disseminated to patient organisations and media.

**Trial registration number:**

NCT05517850.

STRENGTHS AND LIMITATIONS OF THIS STUDYIncludes a full health economics evaluation.Broad inclusion criteria will help generalise the results to a variety of atopic dermatitis cases.Depending on what time of the year the majority of participants eventually will be recruited, it may be difficult to control for seasonal changes in Sweden’s temperate climate.Earlier similar studies indicate a risk of bias for the recruitment of female participants with an advanced education.If the self-guided condition cannot be found non-inferior, this study cannot answer what specific differences between the conditions caused this result.

## Background

### Atopic dermatitis

Atopic dermatitis (AD) is the most prevalent of the inflammatory skin diseases. The primary symptoms of AD are itch, dry skin and rash.^1^ Treatment and prevention generally consist of emollient creams, topical corticosteroids, other local immunosuppressive creams such as calcineurin inhibitors. If topical treatment is ineffective, phototherapy and systemic immunomodulatory treatments are often given.^2^ In addition to dermatological symptoms, people with AD have an increased risk of major depression and anxiety disorders.^3 4^ Furthermore, behavioural and emotional factors may affect AD symptoms. A common reaction to the itching sensation of the skin is the act of scratching, which, while temporarily relieving, can lead to damage to the skin barrier and an aggravated inflammation.^5^ Furthermore, people with AD tend to scratch when they experience anxiety or depressed mood,^6^ possibly as a conditioned behaviour. In addition, avoidance of itch-associated situations is frequently documented, which may lead to avoidance of activities that are otherwise appreciated or important to the patient, which can further affect mental health and quality of life^7^ The impairment of quality of life by AD is comparable to asthma and type 1 diabetes.^2^ The facts that AD can affect mental health, and that behaviour can directly affect AD symptoms, make psychological treatment relevant.

### Educational and psychological interventions for AD

Various forms of educational and psychological support may be available for people with AD. According to structured reviews, studies of educational interventions for AD have often had suboptimal methodology and unclear results, with tendencies towards effect on skin-related quality of life and improved symptoms.^8^ These interventions may be held in a group or individual setting and may be led by physicians, nurses or other professionals. One recent randomised controlled trial (RCT) of an internet-delivered educational and behavioural intervention, including young adults, showed small but significant effects on AD symptoms and secondary measures.^9^

### Internet-delivered cognitive behavioural therapy

Internet cognitive behavioural therapy (ICBT) is a psychological treatment administered over the internet, otherwise similar to regular face-to-face CBT. ICBT usually includes therapist support via a secure digital communication, similar to email. Studies have shown that a clinician spends the equivalent of about 15 minutes per patient and week in ICBT.^10^ ICBT has been suggested to improve cost-effectiveness as well as the availability of evidence-based treatment^11^ and research reviews show that there are no consistent differences in effectiveness between conventional face-to-face CBT and ICBT.^12^ In Sweden, ICBT has been offered in regular care via the Internet Psychiatry Unit in Stockholm since 2007.^13^

Although ICBT has many advantages, there is an unmet need for interventions for people with mild to moderate illness, where a comprehensive and therapist-guided ICBT programme would be an unnecessarily intense level of care, and thus an inefficient use of resources. One solution is to use existing ICBT programmes and simply remove the therapist guidance. Some research has suggested that this has a negative impact on effectiveness, however, there are indications that the amount and type of therapist contact are not decisive^14^ and recent studies have compared therapist supported ICBT and self-guided ICBT and shown that treatment outcome, treatment implementation and treatment satisfaction do not differ between conditions if certain components are present in the self-guided intervention. These components include a stringent clinical process in the form of an assessment and a follow-up interview with a clinician and a high-quality interface.^15 16^

### Internet-delivered cognitive behavioural therapy for AD

An ICBT protocol has been evaluated for AD. The main components were symptom diary, mindfulness and exposure to avoided sensations and situations, with prevention of unhelpful responses, such as scrathing. The treatment showed promising preliminary effects in a face-to-face pilot study, which subsequently was confirmed in a RCT.^17 18^ A digital self-care intervention has been preliminarily evaluated for people with AD, with promising effects.^19^ Digital self-care was based on the ICBT intervention with comparable components. Thus, there is support that CBT can be effective in improving mental health and reducing symptoms of AD, although additional studies are needed. A comparison between the ICBT and reworked digital self-care variants could further contribute to the literature and the results will have implications for implementation.

This is a study protocol of a single-blind non-inferiority RCT, aimed at evaluating the effects of a self-guided CBT programme available via the internet (digital self-care) for people with AD, in relation to a previously evaluated therapist-guided internet-delivered CBT programme (guided care).^18^ The main hypothesis is that digital self-care will be non-inferior to guided care in reducing self-rated eczemic symptoms, as measured by the patient-oriented eczema measure (POEM).^20^ Secondary purposes are to evaluate use of resources and cost-effectiveness of digital self-care compared with guided care, and to investigate potential mediators of symptom improvement.

#### Hypotheses

##### Primary hypothesis

Digital self-care will be non-inferior to ICBT, according to the predefined non-inferiority margin of three points, as measured by the primary outcome (POEM).

##### Secondary hypothesis 1

Digital self-care will be associated with significantly less staff costs than ICBT, in the form of time spent in hours by a licensed psychologist.

##### Secondary hypothesis 2

Digital self-care will be cost-effective compared with ICBT, assessed at 1-year follow-up.

##### Secondary hypothesis 3

Effects on the outcome will be mediated by the amount of time spent by participants on main treatment components.

### Study design

#### Time frame

The first participant was included on 29 November 2022. The first cohort started on 5 December 2022. Post-treatment data collection is expected to finish summer or autumn 2023, with the last follow-up a year after that. The present study is a non-inferiority RCT for adults with AD. Participants randomised to guided care will receive ICBT via the internet, guided by a therapist for 12 weeks. Participants randomised to digital self-care get access to a self-guided CBT-based intervention for 12 weeks. Condition allocation will be 50/50.

The primary end point is at 12 weeks, (ie, post-treatment). The study will also include a 6-month and a 1-year follow-up. One year after treatment conclusion, long-term effects will be evaluated. An overview of the trial design can be seen in figure 1.

**Figure 1 F1:**
[figure not shown]
CONSORT 2010 flow diagram. CBT, cognitive behavioural therapy; CONSORT, Consolidated Standards of Reporting Trials.

The study is approved by the Swedish ethics authority (reg. no 2021-06704-01) and is preregistered at ClinicalTrials.gov. The participants will receive written and verbal information about the study. The participants will digitally sign an informed consent in a secure platform.

#### Participants

Participants will be recruited via advertisements in social media and with the help of relevant patient associations’ mailing lists and websites. Interested individuals with self-reported AD diagnosis may participate following their written consent to the study. Advertisements in different types of social media has the advantage that it reaches different types of people regarding age and gender. In some platforms, it is possible to make the advertisements to only appear for men, if the female percentage should be considered too high, which is something we could consider. In order to minimise false diagnoses, participants will disclose at which point in time they received their AD diagnosis, and if they can recall, at what clinic and by which physician. They will then receive login information to access a secure digital platform, where data from self-assessment scales will be registered. Participation in the study does not involve any change in their regular treatment or medical self-care. Participants will be evaluated by a licensed psychologist in a clinical interview, assessing suitability according to the inclusion criteria and motivation. If a potential participant states that they are interested, knowing that these interventions will require considerable time and effort, that participant is considered motivated.

##### Inclusion criteria

At least 18 years of age with self-reported AD diagnosis. No new types of medications introduced for 6 months prior, with no intention of future change (participants will not be excluded if they change their medication after inclusion). Participants need to be able to understand written and spoken Swedish, have access to the internet and be able to receive telephone calls and text messages.

##### Exclusion criteria

Other disease or condition that has immediate treatment priority over AD. This could be an ongoing demanding treatment of a severe somatic or psychiatric condition. No specific diagnoses are inevitably a cause for exclusion, as potential participants will rather be evaluated on a case-to-case basis.

#### Setting

The trial is conducted at Karolinska Institutet, a medical university in Stockholm, Sweden. Dermatologists involved in the study are also associated with the dermatology clinic at Karolinska University Hospital, in Stockholm, Sweden. Initial assessment will be made by telephone by a clinical psychologist, and both study arms are entirely conducted online, including the collection of self-rated assessments. Participants will be recruited from all parts of Sweden.

#### Power calculation

Based on data from Hedman-Lagerlöf *et al*
17 and Kern *et al,*
19 we expect an in-group effect of about d=0.85 for both interventions. A consultant statistician performed a power calculation. The required sample size was computed based on boot-strapped (5000 simulations) reruns of weekly measured data obtained in the therapist-guided RCT.^17^ The results indicated that a sample size of 174 would be required for 90% power, α=0.05, given a non-inferiority margin of 3 points on the POEM scale and accounting for 10% missing data.

### Planned interventions

#### Usual care

Participants will continue their usual care. According to national guidelines, people with AD should be treated according to a stepped-care model, with emollients and education at the bottom, advancing to cortisone treatments, up to more advanced treatments, such as immunosuppressive and biological interventions. Between individuals, usual care in Sweden can vary greatly. People with AD in Sweden may be treated and followed up at primary or specialist levels. Not all people with AD have regular contact with a physician at all, some have intermittent check-ups, and others may have close and frequent contact. Psychological interventions are not usually available, whereas educational interventions may be available in some regions of Sweden.

#### Guided care

The aim of CBT for AD is to target behavioural and emotional processes, to improve AD symptoms and increase quality of life. The participants read education material, and use worksheets and homework reports. The material is in Swedish and is currently only available to study personnel and participants. This intervention consists of 10 modules and lasts 12 weeks. An introduction provides information about CBT and AD. Participant register itching and scratching behaviours, with the aim to increase awareness of these behaviours. Gradually, the participants are introduced to the proposed active treatment components: mindfulness training and exposure with response prevention. Mindfulness is trained throughout the intervention. The purpose of mindfulness is to increase awareness of emotional and behavioural reaction patterns, and to increase tolerance of aversive inner experiences.^21^ Additionally, mindfulness training may improve stress tolerance. Participants are also trained in self-compassion, to increase understanding of one’s own reactions and to increase the ability to handle difficult situations in the treatment and life.^22^ After practising these fundamental skills, exposure with response prevention is introduced in week 4. Exposure is a controlled way to gradually approach situations that evoke strong emotions or somatic reactions. The purpose is to gain knowledge and experience in how this approach can change one’s perception of unwanted situations, emotions or somatic reactions.^23^ The assumption is that skills learnt from mindfulness practice and self-compassion training helps the patient to conduct exposure exercises. Response prevention means to reduce scratching in these problematic situations in order to reduce itch in the long term. Through this whole process, the participant is guided by a therapist. The therapist may be contacted through a secure internet platform at any time and responds within 48 hours. Participants read the education material, construct exercises to perform, describe their progress in homework assignments and receive feedback from their therapist. During the 12-week period, the participants work at their own pace, and contacts their therapist when necessary. The recommended pace, however, is one module per week, and the therapist contact participants who are inactive. All participants have access to the same treatment material but will construct exposure exercises that fit their specific situation, assisted by the therapist. The therapists will guide participants to make exercises as faithful to the treatment as possible. Participants will report back what they have done. Because therapist and participants never meet, there is no control of whether participants actually perform exercises as they are reported. The study coordinator will offer guidance to other therapists if needed.

#### Digital self-care

As with guided care, the aim of CBT for AD is to target behavioural and emotional processes, to improve AD symptoms and increase quality of life. The material is similar to guided care but shortened. Likewise, participants, read information and perform exercises in their everyday life. As with guided care, the main treatment components are mindfulness and exposure with response prevention, with a specific focus on itch. Participants will be able to practice mindfulness with the help of instructions and examples. Because it may be challenging to construct relevant exposure exercises without the help of a therapist, participants will receive detailed instructions and guidance, and get to choose exposure exercises from a long list of examples. They will also be free to create their own relevant exposure situations within the intervention. Digital self-care consists of eight modules. The only active interventions, mindfulness and exposure are introduced weeks 1 and 2, respectively. From weeks 3 to 7, no new interventions are introduced and participants are advised to continue practising the interventions, but there is a new theme of education each week, to act as inspiration for exercises. The last 4 weeks, the participant is merely advised to continue practice. There is no therapist, but the study coordinator monitors the process and may contact inactive participants. Participants will access the same digital platform as the guided condition. Participants work entirely at their own pace. Modules will be unlocked automatically if 1 week has passed, and all material in the previous module has been read. Participants will report if they have done their assignments, but there is no control if they do as they report.

#### Differences between study conditions

The main differences between the conditions are that digital self-care (A) has contact with a clinician at only two points in time: preintervention and after 8 weeks plus the addition of automated messages, whereas guided care has continuous contact throughout the treatment via text messages on a secure platform and that (B) the treatment text is significantly shortened. Automated emails are sent every week to the non-guided group, consisting of a greeting and some encouraging words relevant to the week’s content. Both groups receive automated text messages at the time of new assessments. Guided care will also have an evaluation from a clinician via telephone at two points in time. Furthermore, digital self-care uses a mobile optimised interface, and have improvements in design aimed to decrease the need of guidance.

#### Therapists

Only the guided group will have therapist contact. The self-guided group will be managed by the study coordinator. The therapists are licensed psychologists specialised in CBT. All therapists have experience in working with somatic conditions and in a text-based format. All therapists will participate in an introductory workshop before treating in the study. The project coordinator will supervise the therapists regularly and on-demand.

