#### Non-inferiority

Change over time will be modelled using mixed-effects linear regression with a random intercept and slope (time). The main outcome POEM will be analysed by the regression on time (baseline to end point), group (digital self-care vs guided care) and the interaction of time and group. We will consider digital care to be non-inferior to therapist guided if the upper bound of the one-sided 95% CI for the time × group interaction (α = 0.05) is within the a priori non-inferiority margin of 3 points on the POEM.^36^ In addition, we will investigate non-inferiority in a sensitivity analysis per-protocol framework with data from patients who will have initiated module 4 or further in either of the study arms. As for interpretation of results, if the two-sided 95% CI does not contain zero, this will be viewed as indicative of superiority of the corresponding treatment. We will estimate Cohen’s d by dividing the time × group coefficient by the pooled observed baseline SD. All primary analyses will be conducted intent to treat. The power calculations allow for 10% missing post-treatment data on the primary outcome at 90% power. If we have more than 10% missing data, we will use multiple imputation before conducting the primary analysis.

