## Ethics and dissemination

The study will be carried out according to the predefined standards of this trial protocol, the Declaration of Helsinki and Good Clinical Practice. This study will be reported according to the CONSORT statement for non-pharmacological trials.^41^ The interventions that will be administered have deemed safe by consultant dermatologists and have been previously evaluated without serious AEs.^18 19^ This study will use the Vancouver criteria for authorship. The results of this study will be published in peer-reviewed scientific journals, be presented to the scientific community at conferences. The results will also be communicated to study participants, patient organisations and clinicians.

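### The primary model has no therapist term although only guided care is delivered by therapists; if outcomes vary by therapist, the non-inferiority test is anti-conservative, and a sensitivity analysis should show whether the conclusion survives

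*Protocol article*

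**What the plan says.** The Therapists section states that "Only the guided group will have therapist contact" and speaks of therapists in the plural; the self-guided group is managed by the study coordinator. The Guided care section describes what the therapist does: helps to construct exposure exercises, gives feedback on homework, answers messages and contacts inactive participants. The Digital self-care section says that this arm has no therapist.

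The Non-inferiority section fixes the primary analysis as "mixed-effects linear regression with a random intercept and slope (time", with fixed effects for time, group and their interaction. The decision rests on the "upper bound of the one-sided 95% CI for the time × group interaction (α = 0.05", compared with 3 POEM points. The article names no therapist effect, no cluster-robust variance and no sensitivity analysis for clustering.

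The Power calculation section says that "a sample size of 174 would be required for 90% power", "given a non-inferiority margin of 3 points on the POEM scale and accounting for 10% missing data". It gives no SD, number of therapists, ICC or design effect.

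**The concern.** This is a partially nested design: one arm is clustered by therapist and the other is not. If some therapists obtain more improvement than others, the outcomes of participants who share a therapist are correlated. The participant-level intercept and slope absorb the size of that variance but not the correlation, so the guided-arm mean change is treated as more precise than it is.

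In a non-inferiority test the error has a direction. A standard error that is too small lowers the upper confidence bound, and a low bound favours the trial's own hypothesis. The Background says that the results will have implications for implementation, so the conclusions are meant to reach beyond the therapists who happened to take part.

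**Working it through.** **Inputs from the article.** N = 174, allocation 1:1, 90% power, one-sided α = 0.05, margin 3 points, 10% missing data. The true difference is taken as 0, because the authors write "we expect an in-group effect of about d=0.85 for both interventions".

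**Inputs assumed.** Number of therapists k = 3 to 10 with equal caseloads; therapist ICC on change = 0 to 0.05.

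**The plan's own figure.** The 174 comes from a bootstrap of earlier weekly data and cannot be reproduced without them. A consistency check is possible. Analysed participants: 174 × 0.9 = 156.6, about 78 per arm. The SD that gives 90% power is 3 / (1.645 + 1.282) × √(78/2) ≈ 6.40. Then SE = 6.40 × √(2/78) = 1.025, and power = Φ(3/1.025 − 1.645) = 0.90. The SD of 6.40 is back-solved, not stated. The error rates below do not depend on it; the power figures do.

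**Formulas**, with n = 78 and m = n/k guided participants per therapist:

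- Design effect in the guided arm: DE = 1 + (m − 1)·ICC
- True SE = SD·√((DE + 1)/n)
- Naive SE = SD·√((2 − ICC·(m − 1)/(n − 1))/n)
- One-sided error at a true difference of 3 = 1 − Φ(1.645 × naive/true)
- Power of the planned analysis = Φ(3/true − 1.645 × naive/true)
- Power with the correct SE = Φ(3/true − 1.645)

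**Worked ends of the range at ICC 0.05.**

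- k = 3: m = 26, DE = 2.25, true SE = 1.306, naive SE = 1.021, ratio 1.280. Error = 1 − Φ(1.645/1.280) = 9.9%. The bound is too low by 1.645 × (1.306 − 1.021) = 0.47 points.
- k = 10: m = 7.8, DE = 1.34, true SE = 1.108, naive SE = 1.024, ratio 1.083. Error = 6.4%. The bound is too low by 0.14 points.

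| ICC | True SE / naive SE (k = 10 to 3) | One-sided error, planned analysis | Power, planned analysis | Power, correct SE |
|---|---|---|---|---|
| 0 | 1.00 | 5.0% | 90% | 90% |
| 0.01 | 1.02–1.06 | 5.3–6.1% | 90–89% | 89–87% |
| 0.02 | 1.03–1.12 | 5.6–7.1% | 89–87% | 88–83% |
| 0.05 | 1.08–1.28 | 6.4–9.9% | 88–84% | 86–74% |

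**Simulation check.** Simulating the 12-week change (40,000 runs per setting) agreed with these error rates to within about 0.4 percentage points. Simulating individual slopes over 13 weekly points (20,000 runs), which is closer to the stated model, gave 6.3–8.7% at ICC 0.05. The inflation is smaller there because the ICC was set on the true slopes (SD 5) and residual error (SD 3) dilutes it. The slope error variance is 9/1.264 = 7.12, so the ICC on estimated slopes is 0.05 × 25/(25 + 7.12) = 0.039.

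**The case against.** The strongest reply is that the harm is conditional. The article gives neither an ICC nor a number of therapists, and several of its features point to a low ICC: guidance is by text, all guided participants have the same material, they work at their own pace, and the therapists share a workshop and supervision. The Background cites about 15 minutes of clinician time per patient and week, and indications that the amount and type of contact are not decisive. At ICC 0 there is no inflation, and at 0.01 it is minor. If inference is limited to these particular therapists, the problem does not arise. All of this stands. It limits the size, but it does not show that the ICC is zero.

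A second reply is that a statistical analysis plan that is not shown may deal with therapist effects. That is possible. The article, however, does not leave the primary model open: it fixes the fixed effects, the random effects, the bound, the margin and a per-protocol sensitivity analysis.

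A reader might infer more than the document supports:

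- **That the error rate definitely exceeds 5%.** This needs a positive ICC, which the article neither states nor excludes.
- **That the planned analysis has only 74% power.** That figure belongs to an analysis with the corrected SE. The planned analysis keeps about 84–90% for ICCs of 0.01 to 0.05, partly because it uses a bound that is too low.
- **That the naive SE is 28% too small.** The true SE is up to 28% larger, so the naive SE is too small by up to 1 − 1/1.280 = 22%.
- **That the plan breaches its reporting commitment.** The article says only that the study will be "reported according to the CONSORT statement for non-pharmacological trials"; it does not say what that statement requires about therapists.

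**Conclusion.** The point holds in conditional form. The design is partially nested, and the stated model has no term for it. Any positive therapist ICC on change makes the time × group standard error too small and raises the false non-inferiority rate above 5%, provided that inference is meant to extend beyond these therapists.

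Over the assumed ranges (3 to 10 therapists, ICC 0.01 to 0.05) the true SE is about 2–28% larger than the naive one. An ICC of 0.05 with three therapists is the unfavourable end of that range, not an expectation. The figures assume equal caseloads; unequal ones would raise the design effect somewhat. A shift of 0.14 to 0.47 points in the bound at ICC 0.05 matters only if the result lies near the 3-point margin, and in that case it can change the conclusion. This supports a sensitivity analysis. It does not show that the primary analysis is invalid or that the sample size must change.

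**What to change.** Record the therapist ID for every guided-care participant and report the number of therapists and their caseloads. Pre-specify a sensitivity analysis of the primary non-inferiority bound with a partially nested model: a therapist random slope on time in the guided arm only, with small-sample degrees of freedom. A therapist random intercept alone would not be enough, because the test is on time × group.

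If there are too few therapists to estimate that variance, recompute the bound at fixed ICCs of 0.02 and 0.05. In either case, state whether the non-inferiority conclusion survives.

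The cost is low. Therapists already register their time, so their identity should be available, and no design change is needed. The downsides are a wider interval in this analysis and an imprecise therapist variance when therapists are few. That imprecision is the reason to keep it as a sensitivity analysis and not to replace the primary model.
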